#### Condition 2: TAU

In the TAU condition, families referred to the outpatient mental health clinic receive the most commonly offered family-based treatment at the clinic. This is a non-manualized systemic integrative family therapy where treatment length varies, but with an observed mean of 14 sessions based on data at the clinic. The exact type of intervention is established in collaboration with the family. In contrast to more individual-based therapies, the child participates in the therapy as well as parents and other family members. The family and the relationships between family members are viewed as critical resources for treating mental health issues [40]. In TAU, there are always two therapists working with each family. The therapists are a part of an interdisciplinary team of clinicians that discuss and receive feedback regarding the therapeutic processes. Recent research conducted by members of our research group has shown that this type of TAU is effective [25, 26]. To obtain a more precise and detailed description of the TAU offered in this trial, we will collect information about the intensity and type of therapy provided by therapists in conjunction with more objective measurements obtained from the medical record/journal.

### Therapists

Therapists in the TAU condition are all qualified mental health professionals employed at the clinic’s family team. The team (*N* = 12) consists of certified family therapists, psychologists, and one psychiatrist.

Five qualified EFST therapists employed on the family team (three family therapists and two psychologists) will conduct the EFST intervention. During the data collection, the EFST therapists will gather monthly for three-hour supervision sessions to discuss video material, dilemmas, technical and ethical considerations, and ensure treatment fidelity.

### Measurements

To investigate the research questions, a combination of evaluations and scores from professionals administering the Schedule for Affective Disorders and Schizophrenia for School-Age Children–Present and Lifetime version (K-SADS PL; [41]) and self-evaluation questionnaires with solid psychometric properties will be used at the time points presented in Table 1. As shown, T0 is at pretreatment, T1 after three months, T2 after six months, and T3 after 12 months. With TAU not being a manualized intervention with a fixed length of treatment, we decided to measure the symptoms of the child 3 months after starting the program. At that time, the EFST treatment is terminated, and TAU has reached the point in treatment (if not ended) where we have reason to believe that the treatment has had an effect.

**Table 1 Tab1:** Measures and timeline of assessment

**Measures**	**T0**	**T1**	**T2**	**T3**
K-SADS	x	x		
SDQ	x	x	x	x
KINDL-R	x	x	x	x
DERS-SF	x	x	x	x
ERPS	x	x	x	x
WAI		x		
SCL-10	x	x		
RWC	x	x		

#### Measures for research question 1

To answer our first research question, *How does the EFST intervention compare to TAU in effectiveness*, we will use both a semi-structured interview and parent, teacher, and self-report measures. Our primary outcome measure is the Schedule for Affective Disorders and Schizophrenia in School-Age Children-Present and Lifetime Version (K-SADS-PL), a semi-structured diagnostic interview conducted by qualified clinicians. The interview will be conducted at T0 and T1 to investigate the presence of one or more mental health diagnoses of the children. A diagnosis will be rated as present or not as described in the interview guide [42]. K-SADS-PL is a semi-structured diagnostic interview used to evaluate current and lifetime episodes of psychopathology in children and adolescents. The measure can be used to evaluate at least 33 psychiatric disorders in children and adolescents [43]. In the proposed study, the K-SADS-PL interview will be conducted with the child and parent together. International studies suggest good validity and reliability of the K-SADS-PL [41, 44, 45], and it is validated for the Norwegian population [43].

Our second outcome measure, the Strength and Difficulties Questionnaire (SDQ) [46], is a 25-item questionnaire completed by parents, children (from 11 years of age), and teachers to assess mental health, peer relations, and prosocial behavior. SDQ will be measured at all time points and takes only a few minutes to complete. International and Norwegian studies found satisfactory reliability and validity, with best results for parent reports and generally lowest performance for self-reports [47–49].

In addition to measuring symptoms and problem areas, we will investigate the children’s perceived quality of life at all time points answered by the parents and children. For this purpose, the 24-item self-report measure Health-Related Quality of Life (KINDL-R) [50] will be used. International and Norwegian studies found satisfactory to good validity and reliability of the measure [51, 52].

#### Measures for research question 2

To answer the second research question, *is there empirical evidence to support the EFST theory that parental increased emotional functioning can predict a decline in children’s mental health symptoms,* we apply three perspectives.

The first perspective, how parents relate to their children's emotions, will be assessed by the 20-item self-report measure Emotion-Related Parenting Styles (ERPS) [53] at all time points. International studies have confirmed the reliability and validity of the measure [54, 55]. Our second perspective, the parents’ emotion regulation, will be assessed by the 18-item self-report measure Difficulties in Emotion Regulation Scale, short-form (DERS-SF) [56] at all time points. International studies have confirmed the reliability and validity of the measure [57].

Our final perspective, parents’ sense of self-efficacy and the strength of their relationship with the child, will be assessed by the relationship with child scale (RWC) of the systemic inventory of change [58] at all time points. International studies have confirmed the reliability and validity of the measure [59, 60].

#### Additional measures

To assess the parents’ mental health, the Hopkins Symptom Checklist-10 (SCL-10) will be used at T0 and T1. SCL-10 is a short form of the longer SCL-90. A large Norwegian study showed that the shorter versions of SCL performed almost as well as the full version [61], and international research has confirmed the reliability and validity of the measure [62, 63].

Due to the fact that alliance is a significant predictor of outcome across ages and treatments [64], it is considered important to determine whether the alliances in the two intervention groups are comparable. To control for alliance in the two conditions, the Working Alliance Inventory (WAI) [65] will be assessed by parents at T1. WAI has been found to have adequate validity and reliability [65].

### Data analyses

To test our first hypothesis that the two conditions are equivalent when it comes to effectiveness, Bayesian growth curve analysis and t-tests will be used to assess the effect of the two arms as compared to each other. Independent sample t-test will be performed on the SDQ to compare the outcome of the two conditions for every five clients included in the study. If strong evidence of difference of the treatment effect is provided with few clients, the data collection can stop. To test our second hypothesis that an increase in parents’ emotional functioning predicts a decrease in mental health symptoms for their children, Bayesian growth curve analyses will be used. Bayesian analysis is preferred because it allows for the specification of models that are appropriate for the data and the capacity to provide estimates and credible intervals for any derived parameter. Additionally, when using Bayesian analysis, credible intervals are not dependent on large-N approximations (as confidence intervals used in frequentist statistical approaches), nor are credible intervals dependent on the type of test being performed (as confidence intervals do in frequentist approaches). Furthermore, Bayesian analysis gives methods for evaluating support for the null hypothesis, not just against it [66]. Moreover, it enables monitoring of data collection to see whether there is sufficient evidence to draw conclusions or if additional data is required [67]. Indeed, there is evidence that within child and adolescent mental health research, conclusions could have been made with smaller sample sizes than what was obtained in many cases [68]. The effect size of interest is the difference in treatment effect between each of the arms in the study. Effect sizes of treatments within our field vary [10, 69], with treatment effects of 0.80 regarded as good. In line with conventional procedures in meta-analyses [65], we consider a difference of 0.40 as meaningful. Based on the experience of research within the clinic, an anticipated drop-out rate of 20% is reasonable [35, 36]. Clinical significant change will be assessed using the method defined by Jacobson & Truax [54]. Missing data will be managed with multiple imputation and all analyses will be performed as intention to treat (ITT).

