## Aims and research questions

Using a randomized controlled trial in routine care, we aim to compare EFST with TAU within an outpatient clinic for child and adolescent mental health (BUP), as presented in Fig. 1. We have two main hypotheses. Our first hypothesis is that the two conditions are equivalent when it comes to effectiveness. Our second hypothesis is that an increase in parents’ emotional functioning predicts a decrease in mental health symptoms for their children.

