## Discussion

With EFST being a newly developed method, there is still a lack of empirical evidence on the effectiveness of this method and a need for RCT studies. The present study will provide important contributions to this field. Despite limited evidence of EFST's effectiveness, it is increasingly being used in outpatient clinics in Norway for child and adolescent mental health. To assess whether the intervention should continue to be offered, it is necessary to conduct an evaluation of its effectiveness. This project will supplement previous research to facilitate evidence-based decision-making in mental health clinics. If it is proved to be as beneficial as TAU, it should be supplied to a greater number of families than is currently the case since it is considered to be an easy to implement and cost-effective treatment with minimal burden to the child. In contrast, if the intervention is determined to be unsuccessful, clinics must consider how it should be used and to whom it should be offered. Additionally, this study will provide insight that may be used to question and broaden the EFST theory regarding the relationship between changes in a parent's emotional process and changes in a child’s mental health symptoms.

Additionally, from a study design standpoint, experiences with data monitoring during data collection can serve as a reference for future research in the field of child and adolescent mental health.

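### Equivalence is the first main hypothesis, but no equivalence region or decision rule is fixed, and the sample size and stopping rule target a difference

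*Protocol article*

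**What the plan says.** Under Aims and research questions the article states: "Our first hypothesis is that the two conditions are equivalent when it comes to effectiveness". Data analyses repeats this and gives the method: "To test our first hypothesis that the two conditions are equivalent when it comes to effectiveness, Bayesian growth curve analysis and t-tests will be used".

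The other design elements concern a difference:

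- **Sample size** (Participants): 60 per condition, from 80% power, an expected effect size of 0.4 and 20% drop-out.
- **Effect size** (Data analyses): "we consider a difference of 0.40 as meaningful". It is not linked to the equivalence hypothesis.
- **Monitoring** (Data analyses): "Independent sample t-test will be performed on the SDQ to compare the outcome of the two conditions for every five clients included in the study".
- **Stopping** (Data analyses): "If strong evidence of difference of the treatment effect is provided with few clients, the data collection can stop". No matching rule is given for equivalence.

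Data analyses also gives reasons for a Bayesian approach. Among them are that it can weigh evidence in favour of a null hypothesis and that it yields credible intervals. No prior, threshold or decision rule accompanies these remarks.

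The Discussion names the consequence: "If it is proved to be as beneficial as TAU, it should be supplied to a greater number of families".

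**The concern.** In an equivalence question the region is part of the hypothesis: without it, the statement under test is undefined. A t-test, or a Bayes factor for a point null, asks whether the difference is exactly zero. Equivalence asks whether the difference is small enough not to matter. A small trial can favour zero over a diffuse alternative and still be compatible with a difference that its own authors call meaningful.

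Wider provision of EFST to families of children with diagnosed disorders is to follow from a favourable answer. The plan does not say what result would count as that answer, or how it would differ from an inconclusive one.

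**Working it through.** **Inputs.** From the article: 60 randomised per arm, 20% drop-out, effect size 0.4 in SD units (so SD = 1). Evaluable at the low end: 60 × 0.8 = 48 per arm. Multiple imputation keeps all 60 in the analysis without restoring full information, so 48 to 60 is the range. Assumed, because not stated: Cauchy prior scale 0.707, threshold BF01 > 3, full sample reached. The calculations apply to the SDQ. No expected diagnosis rates are given, so none is possible for K-SADS.

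**The plan's own figure.** For detecting 0.4 with two-sided alpha 0.05 and 80% power, n = 2 × ((1.960 + 0.842)/0.4)² = 98.1, so 99 evaluable and 99/0.8 = 124 randomised per arm. With one-sided alpha 0.05 it is 78 and 98. The stated 60 is not reproduced. The article cites a Bayesian procedure whose prior and threshold it does not report, so that calculation cannot be checked exactly. For this point it matters only that the figure is aimed at detecting a difference. By comparison, two one-sided tests at ±0.40 (5% each, 80% power, true difference 0) need n = 2 × ((1.645 + 1.282)/0.4)² = 107.1, so 108 evaluable and 108/0.8 = 135 randomised per arm.

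**What null support shows.** With N = n/2, ν = 2n − 2 and prior scale r, BF10 is the integral over g of (1 + Ngr²)^(−1/2) × [1 + t²/((1 + Ngr²)ν)]^(−(ν+1)/2) × p(g), divided by (1 + t²/ν)^(−(ν+1)/2), where p(g) = (2π)^(−1/2) g^(−3/2) e^(−1/(2g)). BF01 = 1/BF10. Solving BF01 = 3 for t:

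| | 48 per arm | 60 per arm |
|---|---|---|
| t at BF01 = 3 | 0.998 | 1.093 |
| observed d = t × √(2/n) | 0.204 | 0.200 |
| 95% half-width | 0.405 | 0.362 |
| 95% interval | −0.20 to 0.61 | −0.16 to 0.56 |
| P(BF01 > 3), true d = 0 | 68% | 72% |
| P(BF01 > 3), true d = 0.2 | 48% | 48% |
| P(BF01 > 3), true d = 0.4 | 17% | 14% |

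The probabilities come from the noncentral t distribution with noncentrality d × √(n/2). At the threshold both intervals contain 0.40.

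**Sensitivity to the prior.** For scales 0.5 to 1.414 the same calculation gives boundary t values of 0.605 to 1.501 (48 per arm) and 0.757 to 1.569 (60). Multiplying by √(2/n) and adding the half-width, the upper limit at the boundary is 0.53 to 0.71 and 0.50 to 0.65. It exceeds 0.40 throughout. P(BF01 > 3) at a true difference of 0.40 is 8–32% and 7–27%.

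**What a region-based rule would give.** Conclude equivalence if P(|difference| < 0.40) ≥ 0.95, with a flat prior, normal approximation and SE = SD × √(2/n). Baseline adjustment with an assumed correlation of 0.6 gives a residual SD of √(1 − 0.36) = 0.8.

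| n per arm, SD | SE | Posterior mass inside ±0.40 at estimate 0 | Met if \|estimate\| below | Chance at true d = 0 |
|---|---|---|---|---|
| 48, unadjusted | 0.204 | 0.94996 | never | 0% |
| 60, unadjusted | 0.183 | 0.972 | 0.093 | 39% |
| 48, SD 0.8 | 0.163 | 0.986 | 0.130 | 58% |
| 60, SD 0.8 | 0.146 | 0.994 | 0.160 | 73% |

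The last column is 2Φ(limit/SE) − 1. At a true difference of 0.40 the rule wrongly concludes equivalence in at most about 5% of trials; for 48 per arm adjusted, Φ((0.130 − 0.40)/0.163) = Φ(−1.65) ≈ 0.05.

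**The case against.** The article does not rely on a bare significance test. It chooses Bayesian methods partly because they can favour a null, it promises credible intervals, and it names a meaningful difference. Equivalence could be judged from an interval set against 0.40. Priors and Bayes factor thresholds are also details that a condensed article may leave to a fuller plan. This stands in part: the planned analysis can be made to address equivalence, and the fault is that the criterion is not fixed. The omission of the region is harder to excuse. The region defines the first main hypothesis, and the article does commit itself on sample size, monitoring and stopping, all in terms of a difference.

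Three stronger readings are tempting, and the document does not support them:

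- *A failure to find a difference will be taken as equivalence.* A reader might infer this, since a t-test at true d = 0.40 is non-significant in 51% (48 per arm) or 42% (60) of trials. The article contains no such rule, and the Discussion requires that benefit be proved. The plan merely does not exclude that reading.
- *Strong evidence for the null cannot be reached at this size.* That depends on an unstated prior and threshold. The largest possible BF01 at 48 per arm runs from 3.5 to 8.9 for scales 0.5 to 1.414. The article asks for strong evidence only when stopping for a difference.
- *Intention-to-treat alone is an error here, so a per-protocol set is required.* No non-adherence or crossover rate is given. TAU is non-manualised, varies in length and may be unfinished at three months, so a per-protocol set would be hard to define. Whether to add one is debatable.

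**Conclusion.** The point holds in this form: equivalence is hypothesised, no region or decision rule for it is fixed, and the sample size and stopping rule address a difference. As written, the plan cannot tell equivalence from insufficient data before the wider provision that the Discussion describes.

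That gap is read directly from the text and needs no assumption. Its illustrated size (an upper limit of 0.56 to 0.61 SD at the threshold, and 14–17% of trials meeting it at a true difference of 0.40) rests on the assumed prior and threshold and on 48 to 60 per arm. The figures move with the prior, but the upper limit stays above 0.40 for every scale from 0.5 to 1.414. This should be settled before analysis, because it determines what the first main hypothesis test can conclude.

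**What to change.** In Data analyses:

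1. State that for the SDQ equivalence means a standardised difference within ±0.40, the article's own meaningful difference, and name the SDQ report and time point to which it applies.
2. Set a separate bound on the proportion scale for the primary outcome, K-SADS diagnosis present or absent. An SD bound does not carry over to it.
3. Base the conclusion on the baseline-adjusted posterior: 'equivalent' only if the probability that the difference lies inside the bound is at least 0.95; 'different' if the 95% credible interval excludes zero; otherwise 'inconclusive'. State which label applies if the first two both hold.
4. State that a non-significant t-test or a BF01 alone does not establish equivalence.
5. Report in advance the chance of each conclusion.

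The cost is mainly wording, plus agreement on a bound for K-SADS. The drawback is that equivalence will often not be concluded even when it is true. For the SDQ at zero true difference the chance is about 58% (48 per arm) to 73% (60) with residual SD 0.8 assumed, and essentially 0% to 39% unadjusted.

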### Participants

Participants will be children referred to the child and adolescent mental health department at Sorlandet Hospital (Abup) in Southern Norway. As a standard procedure at the clinic, regardless of whether one takes part in a research project, all clients (i.e., children) undergo a standardized assessment of their functioning and symptoms of mental distress and developmental history. If, from the initial assessments, it is determined that the client is eligible for a family-based treatment in the family team of the clinic, the children and their parents will be invited to take part in this study. To be eligible, the following criteria must be met: a) the child meets the criteria for a mental health disorder, b) the disorder is assessed by health professionals to be related to parent or family functioning, and c) the families are motivated to work within a family-based framework to improve the suffering of their child and the relational difficulties in the family. The main researcher or the head of the family team will provide participants information about the study in age appropriate ways and go through the written consent form. After consent for participation, each family (one child with one or two parents) will be assigned randomly to one of the treatment conditions using the www.randomizer.org website. Randomization will be requested by the therapist responsible for recruitment and clinical interviews. Based on the clinic’s experience of research, an anticipated drop-out rate of 20% is reasonable [35, 36]. With 80% power, an expected effect size of 0.4, and an anticipated 20% drop-out rate, the number of clients in each condition is calculated to be 60, following a procedure described by Schönbrodt & Wagenmakers [37]. By choosing Bayesian statistics, evidence will be obtained even when the power calculations might be mis specified [38].

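### The SDQ t-test that governs early stopping has no stated baseline adjustment, although SDQ is collected at T0; adjusting for it would gain precision at no cost

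*Protocol article*

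**What the plan says.** Data analyses names two methods for the first hypothesis, that the arms are equally effective: Bayesian growth curve analysis and t-tests. It then describes the repeated comparison: "Independent sample t-test will be performed on the SDQ to compare the outcome of the two conditions for every five clients included in the study". The next sentence gives the consequence: "If strong evidence of difference of the treatment effect is provided with few clients, the data collection can stop". No other analysis is attached to that decision.

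The baseline score is available. Measurements states that "SDQ will be measured at all time points", and Table 1 lists the SDQ at T0, T1, T2 and T3. The t-test is described without a baseline covariate. The text does not say whether it compares post-treatment scores or change from T0, at which time point, or for which informant. Participants describes allocation through a web randomizer and mentions no stratification on baseline severity.

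For scale, Data analyses says "we consider a difference of 0.40 as meaningful", and Participants gives 60 per condition under these inputs: "With 80% power, an expected effect size of 0.4, and an anticipated 20% drop-out rate".

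**The concern.** Hypothesis 1 is a claim of equivalence, so its credibility depends on a narrow interval for the arm difference. Children aged 6 to 18 with a wide range of diagnoses are eligible, so some correlation between a child's SDQ at T0 and at T1 is plausible. A test that leaves this out carries between-child variance that the trial has already measured.

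The SDQ is the secondary outcome; the primary outcome is the K-SADS diagnosis. The SDQ t-test still matters beyond its own result, because it decides when data collection ends and therefore how much data every other analysis receives.

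**Working it through.** **The plan's own figure.** For 80% power at a difference of 0.40 SD, a fixed-sample two-sided 5% t-test needs 2 × (1.960 + 0.842)² / 0.40² ≈ 98, or 99 per arm with the t correction, and 99 / 0.8 ≈ 124 after 20% dropout. The stated 60 per arm is therefore not reproduced this way. It is attributed to a Bayes-factor design procedure whose prior and threshold are not given, so it cannot be rerun. That is a separate matter and is not used below, except that 60 per arm sets the number of completers.

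**Inputs from the protocol.** 60 per arm; 20% dropout, giving 60 × 0.8 = 48 completers per arm; difference of interest 0.40 SD.

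**Assumptions.** T1 scores with the same SD at T0 and T1; a T0-T1 correlation r of 0.3, 0.5, 0.6 or 0.7 (none is given); a single two-sided 5% test as a stand-in for the Bayesian criterion.

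**Standard error of the arm difference, in SD units.**
- Post-treatment t-test: √(2/48) = 0.204.
- Change-score t-test: √(2/48) × √(2(1 − r)).
- ANCOVA: √(2/48) × √(1 − r²).

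Power follows from the noncentral t distribution with 94 degrees of freedom and noncentrality 0.40 / SE. ANCOVA loses one further degree of freedom, which is negligible.

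| r | Post-score SE, power | Change-score SE, power | ANCOVA SE, power |
|---|---|---|---|
| 0.3 | 0.204, 49% | 0.242, 37% | 0.195, 53% |
| 0.5 | 0.204, 49% | 0.204, 49% | 0.177, 61% |
| 0.6 | 0.204, 49% | 0.183, 58% | 0.163, 68% |
| 0.7 | 0.204, 49% | 0.158, 71% | 0.146, 78% |

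The ordering does not depend on the chosen values. ANCOVA beats the post-score test whenever r is not zero. It beats the change score whenever r is below 1, since 2(1 − r) − (1 − r²) = (1 − r)² > 0.

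**Equivalence.** Take 0.40 as an illustrative margin, a true difference of zero and a normal approximation. The chance that a 90% interval lies within ±0.40 is 2Φ(0.40/SE − 1.645) − 1. This is 25% for the post-score test, against 32%, 46%, 58% and 73% for ANCOVA at r = 0.3, 0.5, 0.6 and 0.7.

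**Sequential check.** 8,000 simulated trials used a default two-sample Bayes factor (Cauchy scale 0.707) with looks every 5 clients from 10 to 120, stopping for a difference when the Bayes factor exceeds 6. Prior, threshold and first look are assumed.
- True difference 0.40: the chance of stopping for a difference is about 41% on post-treatment scores, against 45%, 52% and 71% with ANCOVA at r = 0.3, 0.5 and 0.7.
- No true difference: 5.0–5.3% stop falsely without adjustment and 5.3–5.6% with ANCOVA.

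**The case against.** **The growth curve already covers hypothesis 1.** This stands as a limit on the point. The growth curve is one of the two named analyses, and if it includes T0 it uses the baseline. A reader might infer that the whole SDQ comparison for hypothesis 1 ignores baseline, and the document does not support that. The loss belongs to the t-test. That test is nevertheless named as a hypothesis 1 analysis and is the only one tied to stopping.

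**The t-test may be run on change scores.** The wording about a difference in treatment effect permits this reading, and the text does not settle it. On that reading the gain from ANCOVA is smaller at high correlations: about 10 points at r = 0.6 and 7 at r = 0.7, rather than 19 and 28 or 29. It does not vanish, and at r = 0.3 the change score is worse than the plain test.

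**Early looks are at the mercy of chance baseline imbalance.** This stronger reading is tempting. With 10 per arm the baseline difference has SD √(2/10) = 0.45 and exceeds 0.4 SD in about 37% of trials. But that variability is already in the t-test's standard error. Imbalance explains r² of the variance of the unadjusted difference (9% to 49% for r = 0.3 to 0.7), the same share at every look. In the simulation, false stops that did occur usually coincided with imbalance in the same direction (80% to 99%), which would make such a stop awkward to defend. Their frequency was about 5% with or without adjustment.

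**The correlation is unknown and the gain may be small.** True: at r = 0.3 power rises only from 49% to 53%. Every child must meet criteria for a disorder, which may narrow the baseline range and lower r.

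**A condensed article leaves covariates to the full plan.** Often so. Here, however, the article names a specific test and attaches a stopping decision to it, and a better test using data already collected can be named in its place.

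**Conclusion.** The point holds in a limited form. The SDQ t-test that governs stopping, and is one of two analyses named for hypothesis 1, is stated without baseline adjustment. At 48 completers per arm and a difference of 0.40, adjustment raises power from about 49% on post-treatment scores to between 53% and 78%. Against change scores the gain is 7 to 16 points over r = 0.3 to 0.7. These sizes rest on assumed correlations and a fixed-sample frequentist approximation; the direction does not.

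The unadjusted test is valid but inefficient. There is no support for saying that it inflates false stopping or that imbalance drives the early looks, and the growth-curve analysis is unaffected if it includes T0. This is a worthwhile improvement rather than a flaw that invalidates the trial.

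**What to change.** Replace the independent-samples t-test, at each look and in the final t-test comparison, with a Bayesian ANCOVA of T1 SDQ on arm, adjusted for the same informant's T0 SDQ. Using the planned growth model with T0 included would serve equally. State that any stopping decision rests on the adjusted arm effect. The unadjusted t-test can stay as a descriptive supplement.

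The change takes about one sentence in Data analyses. It needs no new data and adds no burden for families.
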